### Cointerventions and Rescue Medication

Any enrolled participants already taking ALA will be weaned off during a pretrial washout of at least seven days. Participants taking and perceiving benefit from opioids (<90 mg morphine equivalents), antidepressants (tricyclic, selective serotonin reuptake inhibitor, or SNRI), NSAIDS, or acetaminophen may continue these medications at a steady daily dose for the duration of the study. Any ongoing cognitive-behavioral therapy and exercise programs perceived as beneficial will be allowed to continue only if it is certain that these will be evenly used throughout the trial. Participants will not be allowed to start new medications, cognitive-behavioral therapy, or exercise programs at any point during the study. Participants will be required to avoid any procedural pain therapies (eg, neurosurgical interventions, nerve blocks, or acupuncture) during the study. Participants will be permitted to take acetaminophen (≤8 tablets, 325 mg/tablet daily) for inadequate pain relief only during the taper and washout phases of each treatment period. Acetaminophen consumption will be recorded as a secondary outcome measure.

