### Outcome Measures

During the trial, the study nurse will contact participants by telephone at least once a week to evaluate adverse effects, assess pain intensity, and encourage compliance. Furthermore, participants will be evaluated in the clinic on 1 of the 5 weekdays of week 4 of each treatment period for vital signs and assessment of secondary outcomes. Finally, participants will be followed up by telephone 2 weeks and 3 months following the completion of the study to document any subsequent problems or adverse events. See Table 1 for the schedule of study assessments.

**Table 1 table1:** Schedule of assessments.

Assessment	Screen	Baseline	Treatment periods			3-Month Posttrial completion
			Weeks 1-3	Week 4	Week 5 (Washout)	
Days per treatment period	−14	−7	1-21	22-28	29-35	
Present pain intensity, 0-10 numerical rating scale (average and worst)	*^b^					
Concurrent medications^a^	*	*	*	*	*	*
Demographics and medical history	*					
Vital signs and weight	*			*		
Clinical biochemistry	*					
Adverse events^a^	*	*	*	*	*	*
Other adverse effects^a^			*	*	*	
Drug dispensing		*		*		
Drug compliance and accountability				*		
Daily pain diaries		*	*	*	*	
Maximal tolerated dose levels			*	*	*	
Medical Outcomes Study-Sleep Scale		*		*		
Patient global impression of change			*	*	*	
Brief Pain Inventory		*		*		
Beck Depression Inventory-II	*	*		*		
Medical Outcomes Study 36-item short-form health survey		*		*		
Rescue acetaminophen^a^			*	*	*	
Fibromyalgia Impact Questionnaire		*		*		
Short-form McGill Pain Questionnaire		*		*		
Blinding questionnaire				*		

^a^Evaluated during weekly participant telephone contacts with research nurse.

^b^* indicates timing of each trial assessment.

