### Sample Size

Statistical considerations underlying this sample size calculation are based on the null hypothesis that there is no difference in pain intensity between the study treatments and the alternative hypothesis that ALA is different from placebo. Systematic reviews of placebo-controlled chronic pain trials consistently reveal that statistically significant treatment-placebo group differences vary between 0.5 and 1.5 points depending on the magnitude of placebo response in any given trial [32]. Thus, on the basis of previous estimates of within-participant variation in fibromyalgia [33], we project that a sample size of 21 participants would provide an 80% chance of detecting (at an alpha level of .05) a mean treatment group difference of 1.5 points on a 0-10 numerical rating scale. In order to have a sample size divisible by 4, we have adjusted the sample size to 24 participants. Accounting for trial dropout rates from our previous trials and for a 2-period crossover design, we expect that the recruitment of 30 enrollees for each trial will yield the above number of completers.

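### Current ALA users can enter on pain rated while taking ALA, and the 4/10 threshold is not applied again after their washout, which tends to lower the ALA–placebo difference among the users admitted

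*Protocol article*

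**What the plan says.** Four parts of the protocol article bear on this point.

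- **Cointerventions and Rescue Medication.** Current ALA use is no bar to entry: "Any enrolled participants already taking ALA will be weaned off during a pretrial washout of at least seven days". The sentence sets a minimum length. It does not say where the washout falls relative to the screening and baseline visits.
- **Participants (inclusion and exclusion criteria).** A participant must have had daily pain of at least 4/10 for three months or longer. The only exclusion that touches ALA is hypersensitivity to a study medication; current use, recent use and earlier failure on ALA are not listed.
- **Outcome Measures, Table 1.** The row that begins "Present pain intensity, 0-10 numerical rating scale (average and worst" is marked in the Screen column (day -14) and nowhere else. Daily pain diaries start at Baseline (day -7), but no entry threshold is tied to them.
- **Randomization and Blinding.** The next consecutive number is given out on enrolment. Since the washout sentence speaks of people who are already enrolled, a literal reading puts numbering before ALA is stopped.

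The Sample Size section supplies the planning figures. Its power statement is "a sample size of 21 participants would provide an 80% chance of detecting". The target effect is 1.5 points and the significance level is .05.

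**The concern.** The pain criterion is meant to find people with enough pain for a drug effect to show. In a person already taking the study drug, the pain it measures is what is left after that drug has acted. A minimum washout of seven days cannot replace a look-back of three months, so for a longer-term user most of the qualifying history lies on ALA, whichever day it is checked.

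The criterion then depends partly on response to ALA. Of two users with the same untreated pain, the one who responds less is more likely to pass. What is at stake is the average ALA effect among admitted users and, through it, the power of a trial planned for 24 completers. The plan foresaw ALA users but did not line up the pain criterion with their washout.

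**Working it through.** **1. Inputs from the Sample Size section.** 21 participants, 80% power, alpha .05, difference 1.5 points. The test is taken as two-sided because the stated alternative is "the alternative hypothesis that ALA is different from placebo". The number of completers is then raised: "In order to have a sample size divisible by 4, we have adjusted the sample size to 24 participants". No standard deviation is printed; the plan refers only to earlier work ("on the basis of previous estimates of within-participant variation in fibromyalgia").

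**2. The plan's own figure.** Without an SD, 21 cannot be reproduced independently, so I solved for the SD of the within-participant difference (SDdiff) that it implies.

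- Normal approximation: SDdiff = 1.5 × √21 / (1.960 + 0.842) = 2.45.
- Noncentral t: SDdiff = 2.33, with either 20 or 19 degrees of freedom to two decimals. The within-participant SD is 2.33/√2 = 1.65.

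With SDdiff = 2.33, power is 80% at 21 and about 85% at 24.

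**3. Does the criterion select on response?** Assumed: untreated pain with mean 5.5 to 6.5 and SD 1.5; individual ALA effect with mean 1.5 and SD 1.0, 1.5 or 2.0, independent of untreated pain. Pain on ALA = untreated pain − effect. Simulated mean effect among users who pass:

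| SD of individual effect | Threshold applied off ALA | Threshold applied on ALA |
|---|---|---|
| 1.0 | 1.5 | 1.06 to 1.23 |
| 1.5 | 1.5 | 0.65 to 0.94 |
| 2.0 | 1.5 | 0.23 to 0.60 |

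Among users with untreated pain of at least 4 and an effect of at least 1.5, between 24% and 58% still pass on ALA. Many responders therefore enter, but fewer than under an off-ALA threshold.

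**4. What it could do to power.** Let f be the share of completers who are such users, and g the fraction of the 1.5-point effect that they keep. Then

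- mean difference = 1.5 × [1 − f(1 − g)]
- variance = 2.33² + f(1 − f) × [1.5(1 − g)]²

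Example with f = 0.10 and g = 0: mean 1.35; variance 5.45 + 0.20 = 5.65; SD 2.38; noncentrality 1.35 × √24 / 2.38 = 2.78; power 76%.

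| Share f (assumed) | Mean, g = 0 | Power at 24, g = 0 | Mean, g = 0.5 | Power at 24, g = 0.5 |
|---|---|---|---|---|
| 0 | 1.50 | 85% | 1.50 | 85% |
| 5% | 1.43 | 81% | 1.46 | 83% |
| 10% | 1.35 | 76% | 1.43 | 81% |
| 20% | 1.20 | 65% | 1.35 | 77% |

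If the variance is held at its planned value, the g = 0 column reads 82%, 78% and 68%. For scale, one participant of 24 is 4% and five are 21%.

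**5. What if people stay on ALA because it helps?** Suppose only those with an effect of at least 1 are still taking it. Their mean effect is 1.5 + s × φ(z)/[1 − Φ(z)], with s the SD of the individual effect and z = (1 − 1.5)/s. This gives 2.01, 2.40 and 2.79 for s = 1.0, 1.5 and 2.0, and an off-ALA threshold leaves these values unchanged. Under the on-ALA threshold the simulated means are 1.73 to 1.82, 1.85 to 1.99 and 1.91 to 2.09. The criterion still lowers the users' mean, but they remain above the planned 1.5.

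**The case against.** A reader might infer that the criterion admits ALA non-responders, rejects ALA responders and so biases the whole trial toward no effect. The documents do not support that, for three reasons.

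- A user whose pain fell from 8 to 5 on ALA is a strong responder and still qualifies. As step 5 shows, people who continue because ALA helps them may respond better than planned even after this selection. The downward pull is relative to a threshold applied off ALA, not necessarily relative to ALA-naive participants.
- Neither the dose nor the duration of earlier ALA use is given. Residual pain on an unknown dose does not show failure under the trial's regimen, and someone who began ALA recently built up most of the three-month history without it.
- Nothing suggests that ALA use is common among candidates; the washout sentence reads as a contingency. At a 5% share, power stays above the planned 80% even if those users get no benefit at all.

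Two further inferences also fail. One is that the baseline data are collected on ALA: a washout started at day -14 can end by day -7, and the primary model under Statistical Analysis has no baseline term. The other is that earlier users will see through the blind: this is speculative, and recognition of ALA could as easily enlarge the apparent effect.

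It can also be said that the timing is read from one mark in Table 1 and one word about enrolment, and that a full protocol may settle it. That is fair as to the day of the check. It does not remove the point, because a look-back of three months reaches into the period of ALA use whenever it is assessed. What stands is that the stated rules admit current users, set no exclusion for recent use, and give no threshold that is applied off the drug.

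**Conclusion.** The point holds as a tendency confined to participants who used ALA for much of the three-month window. Among them, the entry rule favours high residual pain on the study drug and so tends to lower the ALA–placebo difference below what an off-ALA threshold would give. The comparison of ALA with placebo remains a valid randomised comparison for everyone admitted; what may shift is the population in which the effect is estimated, and hence power.

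The size cannot be determined from the documents. The power figures rest on an SDdiff recovered from the plan's own 21 participants, on assumed user shares of 5% to 20%, and on an assumed effect of none or half in those users. Within that range the consequence runs from a loss of about 2 points of power to one of about 20, and the larger losses need about five users without any benefit among 24 completers. This makes the change below a cheap improvement rather than the repair of an invalid design.

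**What to change.** Either of two changes to the eligibility text would be enough.

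1. Add an exclusion for ALA use at any time in the three-month window over which the pain criterion is judged.
2. If current users are to stay eligible, apply the existing 4/10 threshold to their baseline-diary ratings of average pain, using only days after their ALA washout has ended and before a treatment number is assigned. The text should then also say that numbering follows this check.

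The first costs a few candidates. The second costs ALA users a longer interval between screening and the start of treatment. Neither adds an assessment, since the diary is already kept from the baseline visit.

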### Study Treatment Dosing Schedule

ALA active study medication and matching placebo is being supplied by SiSU Incorporated (Burnaby BC, Canada) and encapsulated by Central Medical Pharmacy Inc (Toronto, ON, Canada). During each period of this trial, participants will receive 1 set of capsules (ALA capsules) containing ALA 300 mg or placebo (lactose capsules) to be taken 30 min before meals. Each period will last 5 weeks, with a 4-week treatment period and a 1-week washout period. During week 1 of each treatment period, participants will take 2 capsules before bedtime. During week 2, participants will take 2 capsules at dinnertime and 2 capsules before bedtime. During weeks 3 and 4, participants will take 2 capsules in the morning, 2 capsules at dinnertime, and 2 capsules before bedtime. On the basis of previous studies, we expect virtually all trial participants to tolerate and reach the ceiling dose of ALA 1800 mg/day. However, during this flexible dose titration, the final dose arrived at during the maximal tolerated dose week (week 4 of the treatment period) could be lower than the ceiling dose of 1800 mg, if side effects encountered during the dose titration (eg, nausea) are suspected to be due to ALA. Thus, this trial will not use a forced titration to the ceiling dose of 1800 mg/day. Week 5 would be a complete washout, and participants will take no study medication.

### Outcome Measures

During the trial, the study nurse will contact participants by telephone at least once a week to evaluate adverse effects, assess pain intensity, and encourage compliance. Furthermore, participants will be evaluated in the clinic on 1 of the 5 weekdays of week 4 of each treatment period for vital signs and assessment of secondary outcomes. Finally, participants will be followed up by telephone 2 weeks and 3 months following the completion of the study to document any subsequent problems or adverse events. See Table 1 for the schedule of study assessments.

**Table 1 table1:** Schedule of assessments.

Assessment	Screen	Baseline	Treatment periods			3-Month Posttrial completion
			Weeks 1-3	Week 4	Week 5 (Washout)	
Days per treatment period	−14	−7	1-21	22-28	29-35	
Present pain intensity, 0-10 numerical rating scale (average and worst)	*^b^					
Concurrent medications^a^	*	*	*	*	*	*
Demographics and medical history	*					
Vital signs and weight	*			*		
Clinical biochemistry	*					
Adverse events^a^	*	*	*	*	*	*
Other adverse effects^a^			*	*	*	
Drug dispensing		*		*		
Drug compliance and accountability				*		
Daily pain diaries		*	*	*	*	
Maximal tolerated dose levels			*	*	*	
Medical Outcomes Study-Sleep Scale		*		*		
Patient global impression of change			*	*	*	
Brief Pain Inventory		*		*		
Beck Depression Inventory-II	*	*		*		
Medical Outcomes Study 36-item short-form health survey		*		*		
Rescue acetaminophen^a^			*	*	*	
Fibromyalgia Impact Questionnaire		*		*		
Short-form McGill Pain Questionnaire		*		*		
Blinding questionnaire				*		

^a^Evaluated during weekly participant telephone contacts with research nurse.

^b^* indicates timing of each trial assessment.

The primary outcome is the mean daily “average” pain intensity experienced while on the maximal tolerated dose of ALA or placebo during week 4 (days 22-28). This will be determined from participants’ ratings of their “average pain over the last 24 hours” completed in patient diaries every morning using a numerical rating scale from 0 to 10. Secondary outcomes include: frequency or severity of treatment-emergent adverse effects, Fibromyalgia Impact Questionnaire, Medical Outcomes Study Sleep Scale, Patient Global Impression of Change, Brief Pain Inventory, Beck Depression Inventory-II, Beck Anxiety Inventory, the short form McGill Pain Questionnaire, the SF-36 survey, blinding questionnaires, and acetaminophen consumption. All these outcomes will be assessed at the baseline and during week 4 of each treatment period, except for adverse effects and acetaminophen consumption, which will be assessed weekly during each treatment period. In addition, plasma RNA samples will be collected to search for transcription and protein markers of treatment response.

### Sample Size

Statistical considerations underlying this sample size calculation are based on the null hypothesis that there is no difference in pain intensity between the study treatments and the alternative hypothesis that ALA is different from placebo. Systematic reviews of placebo-controlled chronic pain trials consistently reveal that statistically significant treatment-placebo group differences vary between 0.5 and 1.5 points depending on the magnitude of placebo response in any given trial [32]. Thus, on the basis of previous estimates of within-participant variation in fibromyalgia [33], we project that a sample size of 21 participants would provide an 80% chance of detecting (at an alpha level of .05) a mean treatment group difference of 1.5 points on a 0-10 numerical rating scale. In order to have a sample size divisible by 4, we have adjusted the sample size to 24 participants. Accounting for trial dropout rates from our previous trials and for a 2-period crossover design, we expect that the recruitment of 30 enrollees for each trial will yield the above number of completers.

### Recruitment

One-month lead time will be allowed to begin recruiting study participants. A maximum of 15 participants will be on each treatment period at any given time. On the basis of these factors, our projected trial completion time is 24 months. As we have been doing for our previous and ongoing chronic pain trials [34-37], a concurrent series of participant recruitment methods will be used [38].

### Statistical Analysis

Participants who complete both treatment periods will be included in trial efficacy analyses. When data from only one period are available, sensitivity analysis including all participants will also be performed, by assuming some reasonable but extreme values for the remaining periods. Those receiving at least one dose of study drug will be included in the safety analyses.

The primary outcome will be calculated as an average of pain scores as recorded in the participant pain diaries within the last 7 days (at maximal tolerated dose in week 4 of the treatment), if more than 50% of the information (at least four days) is not missing [39]. Otherwise, mean daily pain will be treated as missing data. Sensitivity analyses on the basis of the average of all available pain scores will also be performed to confirm the results of the primary analysis. A linear mixed model with sequence, period, treatment, and the first order carryover as fixed effects and participant as a random effect [39] will be used to test whether there is any treatment difference among groups and to estimate the least square mean of the mean daily pain intensity for each treatment group, adjusting the carryover and period effects. The pairwise comparison between ALA and placebo will be performed on the basis of the least square means and standard deviations from the linear mixed model. Sensitivity analyses will be performed using a pattern-mixture model [40] on the basis of patterns of missing data so as to check the robustness of results in the case that data may not be missing at random. A Fisher’s Least Significant Difference [41] procedure will be used to adjust the *P* values for ALA versus placebo comparisons.

Secondary outcomes will be analyzed similarly except that (1) only 1 measurement will be analyzed in the last week for the singular measures (ie, final week questionnaires), and (2) the scoring algorithms developed for the Brief Pain Inventory, the Beck Depression Inventory-II, the Beck Anxiety Inventory, and the SF-36 will be first used to derive the subscales or domains within these instruments and the scores on these subscales or domains will be used as response variables in the linear mixed model analysis.

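### The primary efficacy set is restricted to participants who complete both periods, although the planned random-participant model can use one-period data; the resulting bias is probably small, but it is avoidable.

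*Protocol article*

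**What the plan says.** All the relevant text is in the protocol article.

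- Analysis set (Statistical Analysis): "Participants who complete both treatment periods will be included in trial efficacy analyses".
- One-period participants (same section): "When data from only one period are available, sensitivity analysis including all participants will also be performed". The method given there is to fill in the unobserved period, "by assuming some reasonable but extreme values for the remaining periods".
- Model (same section): "A linear mixed model with sequence, period, treatment, and the first order carryover as fixed effects and participant as a random effect".
- Evaluable period (same section): the week-4 mean is calculated "if more than 50% of the information (at least four days) is not missing"; otherwise it is set to missing.
- Data that may not be missing at random (same section): "Sensitivity analyses will be performed using a pattern-mixture model".
- Safety set, for contrast (same section): "Those receiving at least one dose of study drug will be included in the safety analyses".
- Expected losses (Sample Size): the target is 24, and "we expect that the recruitment of 30 enrollees for each trial will yield the above number of completers".

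**The concern.** Whether a participant completes both periods is known only after randomisation and can depend on the treatment received first and the pain experienced on it. The completers in the two sequences may therefore no longer be comparable, and the headline estimate need not be that of the randomised comparison. Enrolling 30 to obtain 24 protects power but does not prevent this selection.

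The restriction is also unnecessary. A linear mixed model with a random participant effect accepts a participant who has one evaluable week-4 mean. If it is correctly specified, it is valid when dropout depends on pain already observed. The completer rule gives up that property in the analysis on which the trial will be judged.

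**Working it through.** **The plan's own figures.** The implied dropout is 1 - 24/30 = 20%, and 24/0.80 = 30 matches the stated enrolment. The 21 participants cannot be reproduced forward because the article gives no SD. Solving backwards (difference 1.5, 80% power, alpha .05 taken as two-sided):

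- Normal approximation: SD of paired differences = 1.5 × √21 / (1.960 + 0.842) = 2.45.
- Crossover t test with 19 df: 2.33, so the within-participant SD is 2.33/√2 = 1.65.

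**Assumptions for the rest.** Within-participant SD 1.64 to 1.65; between-period correlation ρ of 0.3, 0.5 or 0.7; true effect -1.5; every dropout has an evaluable period 1; model with sequence, period and treatment, participant random.

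**Bias.** Let d be the mean period-1 pain of a sequence's completers minus that of everyone randomised to the sequence. If dropout depends on period-1 pain, the completers' period-2 mean shifts by ρd, so their period-1 minus period-2 difference shifts by (1 - ρ)d. The treatment estimate is half the difference between sequences, so

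bias of completers = (1 - ρ)/2 × (d for ALA-first - d for placebo-first).

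The mixed model adds ρ × (all - completers) back to the period-2 mean, and the d terms cancel.

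The total SD is 1.64/√(1 - ρ) = 1.960, 2.319 and 2.994 for the three correlations. Let z be period-1 pain minus the placebo mean, divided by that SD. Three dropout rules were examined:

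1. The same rule in both sequences, logit(p) = -1.2 + 1.5z (overall dropout about 23% to 25%). Numerical integration gives d for placebo-first of -0.637, -0.754 and -0.973, and d for ALA-first of -0.348, -0.456 and -0.666.
   - ρ = 0.3: 0.35 × 0.289 = 0.10
   - ρ = 0.5: 0.25 × 0.298 = 0.07
   - ρ = 0.7: 0.15 × 0.307 = 0.05
2. That rule in placebo-first only, with random 20% dropout in ALA-first (d = 0; overall about 25%).
   - 0.35 × 0.637 = 0.22; 0.25 × 0.754 = 0.19; 0.15 × 0.973 = 0.15
3. Extreme case: all dropouts are the 40% of placebo-first participants with the highest pain (overall 20%), so d = -0.644 × SD = -1.26, -1.49 and -1.93.
   - 0.35 × 1.26 = 0.44; 0.25 × 1.49 = 0.37; 0.15 × 1.93 = 0.29

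Simulation of 30 participants (20,000 runs) agrees: 0.05 to 0.10, 0.14 to 0.22 and 0.30 to 0.44. All shifts are toward the null. The all-data estimate is biased by at most 0.01 in each case. With dropout unrelated to outcome, neither analysis is biased. At a true effect of zero that is the same for everyone, rule 1 makes the two d values equal and the bias is zero.

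The direction is not fixed. With individual effects that vary (assumed SD 1.5, within-participant SD 1.2) around a true mean of zero, simulation gives about -0.13 for completers and -0.05 for the all-data model. The all-data model is not exactly unbiased there, because its common-variance assumption is then slightly wrong.

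**Precision.** With 24 completers the SE is 1.646 × √(2/24) = 0.475. Adding 6 period-1-only participants, 3 per sequence, multiplies the variance by 1 - 0.20 × (1 - ρ)/2.

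| ρ | Variance ratio | SE | Efficiency gain | Power at 1.5 (normal approx.) |
|---|---|---|---|---|
| completers | 1 | 0.475 | – | 88.4% |
| 0.3 | 0.93 | 0.458 | 7.5% | 90.6% |
| 0.5 | 0.95 | 0.463 | 5.3% | 90.0% |
| 0.7 | 0.97 | 0.468 | 3.1% | 89.4% |

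**Model.** Two sequences by two periods give four cell means. Intercept, sequence, period, treatment and first-order carryover are five columns of rank 4, so the listed fixed effects cannot all be estimated. The figures above therefore leave carryover out.

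**The case against.** The strongest defence is that the plan does not ignore these participants. It schedules a sensitivity analysis in everyone and a pattern-mixture analysis, and it sizes the trial on 24 completers, so power already allows for the loss. Under a common dropout rule the bias is under a tenth of the 1.5-point target and well below the SE of about 0.47. The article calls the trial proof-of-concept and does not link dropout to pain. Anyone who leaves before week 4 of period 1 has no outcome that the wider set could recover. All of this stands, and it limits the size of the point. It does not justify making the selected set the primary one when the chosen model does not need it.

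A reader might infer more than the text supports:

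- *That one-period data are never analysed.* They are, in the sensitivity analyses.
- *That the pattern-mixture analysis is left with almost no missing-data pattern.* The text does not confine it to completers. The four-day diary rule can also leave a completer with a missing period mean.
- *That nausea will drive withdrawal from ALA.* The Study Treatment Dosing Schedule section links nausea to a lower final dose, not to leaving the trial, and expects nearly everyone to tolerate the ceiling.
- *That leaving the assumed values unspecified is a defect.* Such values commonly belong in an analysis plan, which is not shown here.

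**Conclusion.** The point holds as a matter of which analysis is primary. The completer restriction conditions on a post-randomisation event and is expected to remove about 6 of 30 enrollees from the headline estimate.

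If dropout follows observed period-1 pain and the true effect is -1.5, the typical bias is 0.05 to 0.10 points toward the null. It is about 0.14 to 0.22 if pain-related dropout occurs in the placebo-first sequence alone, and 0.30 to 0.44 only in a deliberately extreme case. The SD is back-solved, and the correlation and dropout mechanism are assumed. The calculation also gives every dropout a valid period 1, which favours the wider set. The gain in precision is too small to carry the argument, so the case rests on avoidable bias.

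The calculations do not support a general claim that the completer set manufactures benefit. With a uniform null effect and a common dropout rule there is no bias, and a spurious benefit appeared only when varying individual effects were assumed. This is a change the sponsor should make, but it is not a fatal flaw.

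**What to change.** Define the primary efficacy set as all randomised participants with an evaluable week-4 mean in at least one period, analysed as randomised in the random-participant mixed model. Make the completers-only analysis a sensitivity analysis beside the all-participant and pattern-mixture analyses already planned.

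State openly that the primary model contains sequence, period and treatment without carryover, and why: the four terms cannot all be estimated in a two-sequence, two-period design.

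The cost is a change of wording and a little more analysis, with no extra participants, visits or data. The primary estimate will then depend on missing at random, which the planned sensitivity analyses examine. Participants lost before week 4 of period 1 remain outside it, and their number should be reported by sequence.

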### Design

This is a double-blind, randomized, 2-period crossover controlled trial comparing ALA to placebo in adults with fibromyalgia (Figure 1). Each of the 2 treatment periods will be 5 weeks in duration, and the entire trial will be 10 weeks long for each participant. Participants will be randomized to one of the two treatment sequences. The randomization sequence will be generated using the Web-based program—randomization.com (Dallal, Tufts University). Participants in sequence 1 will take active inert placebo capsules during the first 4 weeks of the trial (followed by a 1-week washout period) and will subsequently take active ALA capsules for the next 4 weeks of the trial (followed by a 1-week washout period). Participants in sequence 2 will take active ALA capsules during the first 4 weeks of the trial (followed by a 1-week washout period) and will subsequently take inert placebo capsules for the next 4 weeks of the trial (followed by a 1-week washout period). See Figure 1 for a trial design schematic.

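### The primary model fits sequence and first-order carryover together in a two-period, two-treatment crossover, so the ALA effect is not estimable as written, and dropping sequence to resolve this gives up the within-participant comparison

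*Protocol article*

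**What the plan says.** All references are to the protocol article.

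- **Design:** "This is a double-blind, randomized, 2-period crossover controlled trial comparing ALA to placebo". On allocation: "Participants will be randomized to one of the two treatment sequences". The sequences are placebo then ALA, and ALA then placebo, each with a one-week washout after four weeks of treatment.
- **Outcome Measures:** the primary response is a single figure per participant and period, the mean of the daily diary ratings over days 22-28.
- **Statistical Analysis:** the primary model is "A linear mixed model with sequence, period, treatment, and the first order carryover as fixed effects and participant as a random effect". It is used to test for a treatment difference and "to estimate the least square mean of the mean daily pain intensity for each treatment group, adjusting the carryover and period effects". Carryover is therefore part of the primary comparison and not a side check. The section does not say that a term may be dropped, or that baseline or washout data enter the model. Secondary outcomes are to be analysed in a similar way.
- **Sample Size:** working from within-participant variation, "we project that a sample size of 21 participants would provide an 80% chance of detecting" a 1.5-point difference at alpha .05. The number is then raised to 24 completers, with 30 enrolled.

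**The concern.** A two-sequence, two-period crossover supplies four cell means. An intercept, a sequence effect, a period effect and a treatment effect use all four, and nothing is left for a separate carryover effect. With sequence and carryover both fitted, the model has no unique treatment estimate. First-order carryover can be estimated alongside sequence only in larger designs, with more periods, sequences or treatments.

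This matters because it is the trial's only primary test. Software will either report the contrast as non-estimable or silently drop an aliased column. In the second case the reported effect depends on term order and coding, or on a choice made once the data are in hand. The two ways out are different estimators with different precision, and only one of them matches the basis of the sample size. The same defect carries over to the secondary outcomes.

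**Working it through.** **1. Estimability (no assumptions needed).** Code sequence s = 1 for ALA first, period p = 1 for period 2, treatment t = 1 for ALA, and carryover c = 1 when the previous period was ALA.

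| Cell | intercept | s | p | t | c |
|---|---|---|---|---|---|
| Placebo-ALA, period 1 | 1 | 0 | 0 | 0 | 0 |
| Placebo-ALA, period 2 | 1 | 0 | 1 | 1 | 0 |
| ALA-placebo, period 1 | 1 | 1 | 0 | 1 | 0 |
| ALA-placebo, period 2 | 1 | 1 | 1 | 0 | 1 |

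In every row 2c = s + p − t. There are five columns of rank 4. The null vector (0, −1, −1, 1, 2) has a non-zero treatment entry, so the treatment coefficient is not estimable. Full factor coding, with its own level for no previous treatment, gives the same answer. More participants only repeat these four rows, and the random participant effect does not alter the rank of the fixed effects.

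**2. What each resolution estimates.** Weights are on the cells in the order of the table.

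- Drop carryover: (−0.5, +0.5, +0.5, −0.5), the within-participant crossover contrast. Its expectation is the treatment effect minus half of any differential carryover.
- Drop sequence: (−1, 0, +1, 0), the period-1 difference between the two randomised groups. The mean model is then saturated, so generalised least squares gives these same weights.

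**3. Reproducing the sample size.** The inputs from the Sample Size section are N = 21, power 80%, alpha .05 (taken as two-sided, since the alternative is that ALA differs from placebo) and a difference of 1.5 points. No SD is given, so N = 21 cannot be reproduced independently and the SD has to be back-solved.

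- Normal approximation: SD of the difference = 1.5 × √21 / (1.96 + 0.84) = 2.45; within-participant SD σw = 2.45/√2 = 1.73.
- Noncentral t, 19 df: SD of the difference = 2.33; σw = 2.33/√2 = 1.65, so σw² = 2.708.

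The noncentral t value is used below.

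**4. Precision and power at 24 completers (12 per sequence).** Write ρ for the correlation between a participant's two period means. The document gives no value, so ρ is an assumption.

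- Carryover dropped: variance = 2σw²/n = 2 × 2.708/24 = 0.226; SE = 0.475; power for 1.5 points (noncentral t, 22 df) about 85%.
- Sequence dropped: variance = 4σw²/[(1 − ρ)n]. At ρ = 0.5 this is 4 × 5.416/24 = 0.903; SE = 0.950.
- Ratio of the two variances: 2/(1 − ρ).

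| Assumed ρ | SE, sequence dropped | Variance ratio | Power for 1.5 points | Per sequence for 80% power (normal approx.) |
|---|---|---|---|---|
| 0 | 0.67 | 2.0 | 57% | 19 |
| 0.3 | 0.80 | 2.9 | 43% | 27 |
| 0.5 | 0.95 | 4.0 | 33% | 38 |
| 0.7 | 1.23 | 6.7 | 22% | 63 |

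At n = 21 and ρ = 0.5, power falls from the planned 80% to about 29%.

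**The case against.** The strongest reply is that the power loss needs a step the plan never states. Sequence is listed first among the fixed effects and carryover last. A program that removes the last redundant column would remove carryover and return the standard crossover contrast, with about 85% power at 24 completers. Other software would flag the contrast as non-estimable before any result was reported. On this view the slip is a matter of wording that ordinary practice would put right. This stands in part: the low power figures belong only to the route that drops sequence, and they are not the plan's inevitable result. But the text says the least square means are adjusted for carryover, which the benign route does not do, so the harmful reading cannot be excluded. The primary estimator should not rest on column order.

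A second reply is that the SD and correlation come from outside the document. That is true of the power figures, which are a range and not a forecast; the 80% at n = 21 is there by construction. It does not touch the rank result. Nor does any non-negative correlation rescue the carryover-adjusted route, because the variance at least doubles.

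A third point is that carryover can be estimated in this design if sequence effects are assumed to be zero, as randomisation supports in expectation. That is correct, but it is exactly the route that reduces the treatment estimate to period 1.

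Finally, an analysis plan that is not shown might give the fitted form. The article, however, does not leave the model open: it names one, and that model cannot deliver the stated comparison.

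**Conclusion.** The concern holds, and the primary model must be corrected. As written, the ALA-placebo contrast is not estimable; that follows from the stated design and model alone. If carryover is dropped, the planned within-participant comparison is intact. If carryover is truly adjusted for by dropping sequence, the trial becomes a parallel comparison of about 12 versus 12, and power for 1.5 points falls from about 85% to about 33% at ρ = 0.5 (43% to 22% for ρ from 0.3 to 0.7). These power figures assume σw = 1.65 back-solved from N = 21, a two-sided test, 12 completers per sequence and the stated range of ρ.

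**What to change.** Remove carryover from the primary model. Fit sequence, period and treatment as fixed effects with participant as a random effect, and name the treatment contrast from that model as the primary estimate. With participants who complete both periods it has n − 2 degrees of freedom; a Kenward-Roger adjustment also covers sensitivity analyses that include participants with one period only. Delete the statement that the least square means are adjusted for carryover.

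State that carryover is dealt with by design: the one-week washout and the reading in week 4 put the period-2 outcome at least four weeks after the last period-1 dose (one week of washout plus weeks 1 to 3 of period 2). If a check is wanted, report the sequence contrast and the washout-week diary pain descriptively, with no rule that lets them change the primary analysis. Apply the same model to the secondary outcomes.

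The cost is about one sentence of text. The design, data collection and sample size do not change. The downside is that the primary analysis openly assumes negligible carryover, which the design already relies on.
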